### Treatment Fidelity

We will use several methods to monitor and enhance the reliability of our intervention[53]. Team members will be trained separately as either control interventionists and their CRB raters, or experimental interventionists and their CRB raters. Undergraduate and graduate nursing students will be hired and trained as experimental interventionists, control interventionists, or CRB raters. Training for the experimental interventionists consists of 3 hours of total training: best mouth care practices; explanation of dementia and theory behind threat-reduction techniques; detailed description of categories of CRB; strategies to recognize, prevent, and reduce CRB; and completion of specific instruments. The control interventionists receive 1 hour of didactic training regarding best mouth care practices and completion of specific instruments. The CRB raters receive 5 hours of training: 2 hours in the classroom and 3 hours in a NH. The first didactic hour addresses detailed descriptions of categories of CRB. The second didactic hour involves the correct use of the RTC-r and identifying type and quality of CRB from the training vide. The remaining 3 hours will occur in a NH during the baseline observations of mouth care and corresponding CRB data collection. The CRB raters will each complete one 3-hour period with either the PI or the project director (PD) during the 7-day observation period. At the conclusion of the 3-hour period, the CRB rater must have 90% agreement with either the PI or the PD; failure to reach 90% will result in retraining using the 2-hour didactic content and another 3-hour simultaneous data collection period until 90% is reached.

A treatment fidelity checklist will be used by the PD to monitor delivery of the intervention. The checklist contains components of the MOUTh intervention protocol, followed by "yes" (properly perfomed), "no" (not properly performed or incorrectly omitted), or n/a (not applicable). Ten percent (10%) of the mouth care sessions between experimental interventionists and NH subjects will be randomly rated. Retraining of the experimental interventionist will occur if any component of the MOUTh intervention protocol is not properly followed or is omitted. Additionally, experimental interventionists will complete the same treatment fidelity checklist if the MOUTh intervention was not delivered according to protocol. The PI and PD will monitor receipt of the intervention using measures for subject participation in the protocol: intervention dose (duration of mouth care session) and frequency (number of times mouth care completed). These methods and measures will help the team to monitor and ensure the reliability of the MOUTh intervention, its delivery, and its receipt.

### Instruments and Measures

The schedule for data collection is listed in Table 1 located at the end of the manuscript.

***Resistance to care ***is a dependent variable for specific aim #1 and hypothesis H1 and a mediating variable for specific aim #2 and hypothesis H2. It will be measured using a refinement of the Resistiveness to Care Scale, which was developed specifically for use with persons with dementia[54]. The original instrument listed 13 behaviors. Each behavior was rated according to duration and to intensity (mild, moderate, or extreme). The original instrument was designed to be used with videotapes; thus, each behavior was recorded once and the duration for all episodes was measured using time in categories (0 = none, 1-16 seconds = 1; 17-59 seconds = 2; 1-2 minutes = 3; more than 2 minutes = 4). The original RTC was developed and tested using 68 subjects at three sites (311 observations), with α = 0.82 and Kappa values ranging from 0.82 to 0.92[54].

In our pilot study, videotaping mouth care was problematic because of confined space issues (small bathrooms) and privacy concerns[35]. As noted in the pilot study,[35] the RTC was refined and tested for this study. The refinements included removing the duration component, measuring the intensity for each individual behavior, counting the frequency of each behavior within the intensity category, summing all episodes of CRB, and then standardizing the scores by dividing the sum with the duration of mouth care (in minutes) to obtain the rate of CRBs[35].

***Oral health ***of NH residents, a dependent variable attached to specific aim #2 and hypothesis H2, will be operationalized as the total score obtained from the Oral Health Assessment Tool [OHAT]. The OHAT is a modification of the Brief Oral Health Status Examination,[55] an oral health instrument developed specifically for NH residents with moderate to severe dementia. Each of the OHAT's eight categories is pertinent to specific oral structures and is scored from 0 (healthy) to 2 (unhealthy), resulting in a score ranging from 0-16. Internal consistency was obtained using test-retest percent agreements and Intra-carer and inter-carer correlation coefficients for total scores[56]. Intra-carer total OHAT scores achieved a correlation coefficient 0.78 (P < 0.001); inter-carer total OHAT scores achieved a correlation coefficient of 0.74 (P < 0.001). Validity was determined by comparing each of the eight categories with accepted dental criteria and instruments using clinical examinations by a qualified dentist[56]. Oral health assessors blinded to the specific aims of the study and subject assignment will collect this data per the schedule presented in Table 1.

***Functional status ***is a co-variate to CRB because CRB increases with higher levels of functional dependence[57,58]. This variable will be operationalized as the total score obtained from the Katz Activities of Daily Living (ADL) Index. The Katz ADL Index assesses overall performance in six areas of self-care: bathing, dressing, toileting, transferring, continence, and feeding[59]. A score of 1 (completely dependent), 2 (requires assistance) or 3 (completely independent) is assigned for each of the six areas, with scores ranging from 6 (completely dependent) to 18 (completely independent).

***Cognitive impairment ***is a co-variate to CRBs because CRB increases exponentially as cognitive impairment progresses[60]. This variable will be operationalized as a score of 2 or greater on the **Global Deterioration Scale (GDS)**. This instrument is used to quantify dementia severity by placing it in one of seven stages: (1) no cognitive decline-normal, 2) very mild cognitive decline-forgetfulness, (3) mild cognitive decline-early confusional, (4) moderate cognitive decline-late confusional, (5) moderately severe decline-early dementia, (6) severe cognitive decline-middle dementia, and (7) very severe cognitive decline-late dementia[61]. Other researchers have noted correlations from 0.88 - 0.91, P < .05 over six data collections with the Alzheimer's Disease Assessment Scale (ADAS)[62]. The data from the GDS will be used to identify relationships between the severity of cognitive decline and CRBs. The **Mini-Mental State Examination, MMSE**[49] will be used to determine capacity for consent and will be obtained once, during the consent process.

***Demographic data, co-morbidities***, and ***use of psychoactive medication ***are control variables that will be collected from the medical records at baseline. *Demographic data *are necessary for comparisons between control and experimental subjects. Co-morbidities will be collected using the *Charlson Co-morbidity Index*,[63] a weighted index that takes into account the number and seriousness of co-morbid diseases, to calculate a co-morbidity score for each subject. *Use of psychoactive medication *will be calculated from the medical records. Actual received dosages of regularly scheduled and "as needed" anti-depressant medication and anti-psychotic medication will be summed for each subject daily for the 7-day observation period and the 21-day intervention period. Both co-morbid diseases and psychoactive medication use may explain fluctuations in CRBs during the study.

***New infections***. Medical records will also be examined weekly for any new diagnosis of infection (e.g., urinary tract infection, pneumonia), and such infections will be recorded as bivariate data. This variable is a mediating variable for CRB. The "new infection" variable will be used as a control variable for RTC-r scores.

***Time ***is an independent variable that will be incorporated into statistical models to determine the effect of the intervention on CRB and oral health status over specified temporal intervals and shifts (day and evening).

***Dosage ***and ***frequency ***of the intervention are independent variables that will be incorporated into statistical models to determine the effect of the intervention on CRB and oral health status, and to compare the efficacy of the intervention to standard mouth care. Dosage will be calculated by the observer, using a stopwatch to measure the duration of each mouth care session. Dosage is also used to calculate the rate of care-resistance using the RTC-r. Frequency will be measured by counting the number of times mouth care was completed; percentage of completed mouth care will be calculated for each NH subject by dividing the number of successful mouth care completions by 42 (twice daily mouth care for 3 weeks).

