This protocol is innovative in specifically addressing threat perception and fear responses in individuals with dementia who are unlikely to have sufficient contextual or cognitive control over threat perceptions due to altered neurological structures and functions. The specific strategies proposed here are expected to reduce perceptions of mouth care and caregiver as threatening and, in turn, limit or prevent CRBs associated with automatic and reflexive fear responses.

In summary, there is a tremendous gap in knowledge regarding interventions designed to prevent and reduce CRB during mouth care in order to improve the oral health of persons with dementia. Persons with dementia and CRB have been systematically excluded from intervention studies developed to improve oral health among NH residents, even though older adults with moderate to severe dementia have worse oral health those with no or mild dementia. Interventions to address oral health outcomes for NH residents with moderate to severe dementia, and who resist care, have not been systematically examined in either nursing or dental research studies. In order to improve nursing clinical practice and to address oral health disparities, it is imperative to design studies that focus on these interventions.

The purpose of this study is to determine whether CRBs can be reduced, and oral health improved, through the application of an intervention based on the neurobiological principles of threat perception and fear response. **The primary specific aims of the study are to:**

1. Evaluate the efficacy of the Managing Oral Hygiene Using Threat Reduction (MOUTh) intervention for reducing CRBs in persons with dementia;

2. Validate the overall efficacy of the MOUTh intervention using nurse-sensitive oral health outcomes-- swollen and bleeding gums, cleanliness of the oral cavity, saliva, and integrity of the lips and oral mucosa; and

3. Calculate the cost of the MOUTh intervention.

The hypotheses based on the specific aims are as follows:

H1. Implementation of the MOUTh intervention will significantly reduce CRBs during mouth care compared to usual mouth care;

H2. The MOUTh intervention will improve oral health in older adults with dementia through the resolution of swollen and bleeding gums, improved cleanliness of the oral cavity, and the resolution of dry, cracked, and fissured oral mucosa and lips compared to usual care.

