### Description of the MOUTh Intervention

The MOUTh intervention was developed and pilot-tested in a previous study[35]. It contains three components: best mouth care practices for older adults with natural dentition and dentures[36-40]; recognition of CRB[16,41]; and strategies to reduce threat perception during the provision of mouth care[35,36,40,42-44]. The mouth care protocol integrates best mouth care practices with threat reduction strategies derived from the neurobiological, nursing, and dental literature. For example, best mouth care practices included using warm water for rinsing and using interdentate brushes for flossing[36-40]. Threat reduction strategies are a constellation of techniques congruent with previously cited neurobiological and nursing studies. These techniques, which were culled from extant literature as well as from techniques that were successfully employed in a previously published pilot study[35], include interventionist behaviors designed to minimize threat appraisal, such as smiling and relaxed demeanor,[45] distraction, bridging (having an elder hold a toothbrush while the interventionist brushes the elder's teeth), and cueing (the use of polite, one-step commands)[40,42]. Interventionists are trained to encourage the elder to do as much of his or her mouth care as possible. The rationale for this technique is that self-care is unlikely to be perceived as threatening[45]. Experimental interventionists are also trained to avoid the use of "elderspeak," a term used to describe "baby talk" speech patterns associated with infants and pets but inappropriately employed when engaged with older adults: high pitch, short sentences, sing-song cadence, patronizing tone, use of collective pronouns, and infantilizing terms (baby, honey, dearie)[43,44]. Elderspeak is a documented trigger to CRB[43,44] because its dehumanizing approach heightens threat perception.

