### Description of Usual Care

Usual mouth care is a challenging issue. For many persons who resist care, "usual" mouth care may mean NO mouth care[27]. Designing a study in which a potentially powerful intervention is compared to an absence of care would be meaningless. In order to have parity between the control and experimental groups, members of both will receive mouth care from interventionists from the research team. The difference will be that the control interventionists will NOT receive training in techniques designed to prevent and reduce CRB. Instead, the control interventionists will receive training separate from the experimental interventionists. That training will consist of best mouth care practices specific to older adults[36-40]. For consistency, both subjects in the control and experimental groups will receive the same mouth care supplies during the duration of the study: Biotene™ toothpaste (dentate); Biotene™ alcohol-free mouthwash (both); soft toothbrushes (dentate); denture brushes (dentures); interdentate sticks (dentate); denture cleansing paste (denture); and denture cups.

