### Statistical Analysis

Individual growth models using multilevel analysis will be used to estimate the efficacy of the intervention for reducing CRBs in persons with dementia, and to estimate the overall efficacy of the intervention using oral health outcomes. Multilevel models (also referred to as hierarchical linear models) will be used because repeated observations of participants are nested within nursing homes[48,64-68]. Multilevel models deal with the "unit of analysis" problem that face nested studies, that is the units of analysis are not independent, but instead the observations are clustered[48,66,69,70]. Because multiple observations are nested

within participants (i.e., repeated measures), individual growth models will be used. Among the advantages of using individual growth models are the ability to deal with an unequal number of measurement occasions among individuals and heterogeneity of variance[48,65,66,71].

Three-level multilevel models will be estimated for CRBs and oral health outcomes in which the first level is the date/time at which the behaviors or outcomes are observed; the second level is the participant; and the third level is the NH in which the participant resides. Explanatory variables to be included at the first level are dosage; frequency; time; and a dummy variable for baseline versus intervention. Explanatory variables to be included at the second level are a dummy variable for whether the participant is in the intervention group or control group; functional status; cognitive impairment; demographic data (gender, ethnicity, race, age, duration of stay in a nursing home); co-morbid conditions; and the use of psychoactive medications. Variables are discussed and defined above.

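### The H1 outcome is a rate per minute whose denominator, session duration, is post-randomization and also a covariate in the same model, so a lower rate need not mean fewer care-resistant behaviors

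*Protocol article*

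**What the plan says.** All places are in the Protocol article.

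- **Hypothesis** (Background, H1): "Implementation of the MOUTh intervention will significantly reduce CRBs during mouth care compared to usual mouth care". No unit of time is mentioned.
- **Outcome** (Instruments and Measures, resistance to care): the refined scale sums all CRB episodes in a session, "standardizing the scores by dividing the sum with the duration of mouth care (in minutes) to obtain the rate of CRBs". This variable "is a dependent variable for specific aim #1 and hypothesis H1 and a mediating variable for specific aim #2 and hypothesis H2".
- **Denominator** (Instruments and Measures, dosage): the observer times each session with a stopwatch, and "Dosage is also used to calculate the rate of care-resistance using the RTC-r".
- **Duration as treatment received** (Treatment Fidelity): receipt is monitored through "intervention dose (duration of mouth care session) and frequency (number of times mouth care completed").
- **Duration as covariate** (Statistical Analysis): "Explanatory variables to be included at the first level are dosage; frequency; time; and a dummy variable for baseline versus intervention". The models are multilevel, also called hierarchical linear models.
- **What could change duration** (Description of the MOUTh Intervention): "Interventionists are trained to encourage the elder to do as much of his or her mouth care as possible". One-step cueing, bridging and distraction are listed as well. The article does not say what these do to session length.

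**The concern.** One post-randomization quantity has three roles: measure of treatment received, denominator of the outcome, and adjustment variable in the model for that outcome. Three difficulties follow.

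1. **Rate and count can disagree.** If MOUTh changes how long sessions last, the rate moves even when the resident resists just as often. H1 is worded as fewer behaviors.
2. **The adjusted treatment effect is hard to interpret.** With dosage in the model, the group coefficient compares sessions of equal length. Randomization does not protect that comparison, because length is measured after assignment and may depend on it. The outcome is also a curve in duration (count divided by minutes), while the covariate, as listed, enters as a plain linear term.
3. **Very short sessions get extreme values.** One CRB in 20 seconds scores 3 per minute, while ten CRBs in ten minutes score 1 per minute. In a linear model for the ratio, the sessions with least information can carry most weight.

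At stake is what a positive H1 result would mean. The same variable also serves as the mediator for H2.

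**Working it through.** **The plan's own figures.** 60 / (1 − 0.25) = 80 recruited, and 60 × 42 = 2,520 observations. Both reproduce, and this point challenges neither. They set the size of the simulation below.

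**Inputs the article does not give.** Session length by arm, CRBs per session and the frequency of early stopping are not stated. The assumptions are a control median of 5 minutes, 5 CRBs per session, and MOUTh sessions 0 to 100% longer.

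**Step 1: arithmetic of the ratio.** Rate ratio = count ratio / duration ratio. With equal counts and MOUTh sessions longer by a fraction L, it is 1 / (1 + L):

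| L | Unadjusted rate ratio | Count increase that would leave the rate unchanged |
|---|---|---|
| 10% | 1/1.10 = 0.91 | 10% |
| 25% | 1/1.25 = 0.80 | 25% |
| 50% | 1/1.50 = 0.67 | 50% |

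**Step 2: does the planned dosage covariate correct this?** Simulated trials had 30 residents per arm and 42 sessions each. Poisson counts had the same distribution in both arms, with a between-resident SD of 0.5 on the log scale. Durations were log-normal (log SD 0.35), and there were 150 trials per setting. The unadjusted analysis compared resident means. The adjusted one was a random-intercept model with duration as a linear covariate. False benefit means two-sided p < 0.05 favoring MOUTh.

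| L | Group difference (CRBs/min), no dosage | Group difference, with dosage | False benefit, no dosage | False benefit, with dosage |
|---|---|---|---|---|
| 0 | 0.007 | 0.007 | 3% | 3% |
| 25% | −0.243 | −0.039 | 37% | 5% |
| 50% | −0.400 | −0.075 | 79% | 4% |
| 100% | −0.605 | −0.179 | 100% | 28% |

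The control mean was about 1.2 per minute. The covariate leaves 0.039/0.243 = 16%, 0.075/0.400 = 19% and 0.179/0.605 = 30% of the artefact. The Monte Carlo standard error near 5% is √(0.05 × 0.95/150) = 1.8 points. Across this and repeat simulations of the same design, false benefit was:

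- 25% longer: 28–37% without dosage, 4–5% with it
- 50% longer: 69–81% without, 4–11% with
- 100% longer: 98–100% without, 25–31% with

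**Step 3: sessions cut short.** Assume no lengthening, but 15% of control and 5% of MOUTh sessions last only 0.3 to 1 minute, with counts still equal. Taking those short durations as uniform, the mean of 1/duration is ln(1/0.3)/0.7 = 1.72. For an ordinary session it is exp(0.35²/2)/5 = 0.213.

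- Control: 0.85 × 0.213 + 0.15 × 1.72 = 0.439
- MOUTh: 0.95 × 0.213 + 0.05 × 1.72 = 0.288
- Ratio: 0.288/0.439 = 0.66 (0.65 in simulation)

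False benefit was 73% without dosage and 29–36% with it. Adding 50% lengthening to this pattern gave 94% without dosage and 0% with it. The adjusted result thus swings with the pattern of session lengths while counts stay the same.

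**Limits.** Step 3 gives a cut-short session the same count as a full one. If such sessions contain fewer CRBs, the distortion is smaller. The simulations omit the nursing-home level, the growth terms, the baseline phase and the other covariates.

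**The case against.** **Dividing by exposure is ordinary practice.** The refinement comes from the pilot, and H1 speaks of behaviors during mouth care, which is compatible with a rate. If CRBs accrue in proportion to time, the rate is undistorted and the count misleads: a true 20% lower rate in sessions 25% longer gives a count ratio of 0.80 × 1.25 = 1.00. This stands. It argues for showing both measures and against making the count a condition for H1.

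**The planned model already contains dosage.** This also stands in part. The 20% and 33% reductions in the unadjusted ratio cannot be presented as the false effect of the planned analysis, because at those lengthenings the covariate removes most of it. What remains is steps 2 and 3 above, and the difficulty of adjusting for a post-randomization variable that is also the denominator.

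**Stronger readings the article does not support.**

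- A reader might infer that MOUTh is likely to lengthen sessions. No duration is given for either arm, and less resistance could shorten them.
- A reader might infer that refused sessions have zero duration, so that the worst sessions drop out. The article does not say so. An attempt stopped early has a short positive duration and gets a high rate. The remark that usual "mouth care may mean NO mouth care" concerns nursing-home staff care, which both arms share during the 7-day baseline. It does not show missing sessions that differ by arm in days 8 to 28. A scoring rule for refusals may sit in the full protocol, so its absence here is no finding.
- A reader might infer that equal residual variance is imposed. The article cites handling of unequal variance as a reason for choosing growth models, and such details commonly belong to the SAP.

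**Conclusion.** The point holds as a mismatch between hypothesis, outcome and model. H1 claims fewer CRBs, the outcome is CRBs per minute, and the minutes are post-randomization and adjusted for again. A lower rate, adjusted or not, does not by itself show less resistance.

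The size depends on facts the article does not give. The planned adjustment contains most of the problem if session lengths differ moderately between arms. It leaves a false-benefit rate of roughly a quarter to a third if MOUTh sessions double in length or if early stopping is more common in controls. Fewer aborted sessions would be a real gain, but a gain in completion, which the article measures separately.

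The change is worth making before the data are analysed. The point does not invalidate the design.

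**What to change.** 1. Replace the linear model for the ratio with a log-link negative-binomial mixed model for the session CRB count, keeping the planned nesting. Fit it in two forms: per attempted session with no offset, and per minute with log duration as offset.
2. Do not also adjust the H1 treatment effect for dosage.
3. Report session duration and completion by arm beside the H1 result.
4. Reconcile H1 with the outcome definition, and word the conclusion to match the measure (rate or count) that shows the effect. Agreement of both need not be required.

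In the equal-count scenarios checked, the per-session count analysis without dosage kept false benefit at 5% or less.

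Cost: count and duration are already recorded, so only analysis wording changes, plus one extra analysis. The H1 conclusion may be less simple if rate and count disagree.

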Subjects will be recruited according to the following **inclusion criteria: **English-speaking; age 65 or older; documented diagnosis of dementia, Alzheimer's disease, vascular dementia, or Lewy body dementia; identified by NH staff as resistant to mouth care; at least 2 adjacent teeth AND/OR daily wearing of at least one denture plate; the ability to hold a toothbrush; and the ability to move his or her hand to his or her mouth. Once subjects are identified, consent will be obtained initially from the responsible party. After consent is obtained, subjects will be tested using the Mini-mental Status Examination (MMSE)[49]. Those with scores 18 or higher will be evaluated for the capacity to sign a consent form using a modification of Resnick et al.'s Evaluation to Sign Consent instrument[50]. This evaluation includes 8 questions that assess understanding of the study. Participants with dementia must score at least 6 out of the 8 questions correctly in order to sign the consent form. If the elder is deemed unable to sign the consent form assent will be obtained during each interaction between the NH resident and any member of the research team. **Exclusion criteria **are: age less than 65; no documented diagnosis of dementia; inability to hold a toothbrush; inability to raise his or her hand to his or her mouth; receiving treatment for an active dental or denture problem; or a diagnosis of dysphagia requiring thickened liquids.

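### As defined (GDS 2 or above), the cognitive-impairment covariate would be met by essentially every eligible resident and could not represent severity

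*Protocol article*

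**What the plan says.** All references are to the protocol article.

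- **Definition (Instruments and Measures).** Of cognitive impairment: "This variable will be operationalized as a score of 2 or greater on the" Global Deterioration Scale. The stages run from "1) no cognitive decline-normal, 2) very mild cognitive decline-forgetfulness" up to "5) moderately severe decline-early dementia, (6) severe cognitive decline-middle dementia, and (7) very severe cognitive decline-late dementia".
- **Reason for the covariate (same paragraph).** "CRB increases exponentially as cognitive impairment progresses". The paragraph adds that GDS data will be used to study how severity of decline relates to CRB.
- **Entry (Recruitment, Sample, Sample Size).** Residents need a "documented diagnosis of dementia, Alzheimer's disease, vascular dementia, or Lewy body dementia"; "no documented diagnosis of dementia" is an exclusion. No GDS value is an entry criterion.
- **Model (Statistical Analysis).** The level-2 variables include "functional status; cognitive impairment; demographic data (gender, ethnicity, race, age, duration of stay in a nursing home"), and the paragraph closes: "Variables are discussed and defined above". The model therefore takes its variables from Instruments and Measures.
- **Schedule (Table 1).** The GDS is rated once, at the pre-observation baseline.

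**The concern.** A covariate can adjust only for something that differs between participants. The cut at 2 separates stage 1, labelled normal, from everything else, in a trial that admits only people with diagnosed dementia. Early and late dementia receive the same value.

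Two things are at stake. The model would list an adjustment for cognitive impairment that in practice does little or nothing, although the protocol regards severity as a strong driver of CRB. And the stated question about severity and CRB could not be answered from the variable as defined. Severity is likely to vary in this sample, since the consent procedure provides both for residents scoring 18 or higher on the MMSE and for those who cannot sign. Randomisation is blocked by home and time, not by severity, so the model is the only place where severity is handled.

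**Working it through.** **Sample size, for context.** 12 × 5 = 60 evaluable residents; 60 / (1 − 0.25) = 80 recruited; 60 × 42 = 2,520 observations. These reproduce the protocol's figures, and the point does not affect them.

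**Who meets the cut.** Stages 2 to 7 meet it; only stage 1 does not. By the protocol's labels dementia occupies stages 5 to 7. A participant would fail the cut only if a resident with charted dementia were rated normal on the GDS.

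**Information in the indicator.** With k of 80 residents at stage 1, variance = (k/80)(1 − k/80). The protocol gives no GDS distribution, so k is assumed.

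| k at stage 1 | Variance |
|---|---|
| 0 | 0 |
| 1 | 0.0125 × 0.9875 = 0.012 |
| 2 | 0.025 × 0.975 = 0.024 |
| 4 | 0.05 × 0.95 = 0.048 |

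At k = 0 the design matrix (intercept, arm, indicator) has rank 2 of 3, so the coefficient cannot be estimated. At k = 1 to 4 it can, but it rests on those few residents and still does not distinguish stage 5 from stage 7.

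**Information in the stage itself.** The matrix (intercept, arm, stage) has rank 3 of 3. Two assumed mixes:

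- Stages 5/6/7 at 20/50/30%: mean 6.1; variance = 0.2 × 1.21 + 0.5 × 0.01 + 0.3 × 0.81 = 0.49.
- Stages 2 to 7 evenly spread: variance = (6² − 1)/12 = 2.92.

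**What this could cost in precision.** The document gives no correlation between GDS and CRB, so this is illustration only. Suppose stage explains R² = 0.10 to 0.20 of between-resident variation in CRB.

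- *No use of baseline CRB and no other covariates:* SE ratio = √(1 − R²) = 0.95 to 0.89, a reduction of 5% to 11%. This is a ceiling under the assumed R².
- *Effect estimated conditional on baseline CRB:* let baseline and follow-up means correlate at ρ = 0.5 to 0.7 (assumed), with the same R² for each. The squared partial correlation of stage with follow-up is R²(1 − ρ) / [(1 + ρ)(1 − R²)].
  - R² = 0.10, ρ = 0.7: 0.030/1.53 = 0.020, so the SE falls by about 1%.
  - R² = 0.20, ρ = 0.5: 0.100/1.20 = 0.083, so the SE falls by about 4%.

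The second case is closer to this design. Each resident contributes up to 2 × 7 = 14 CRB observations before the intervention, and the model contains a baseline-versus-intervention term. Any overlap of severity with functional status, co-morbidity, medication, age and length of stay would shrink the gain further.

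**Chance imbalance.** With 30 per arm, the SD of the difference in mean stage is √(2/30) = 0.26 SD of the covariate. In outcome terms that is √R² × 0.26 = 0.08 to 0.12 SD of between-resident CRB, before any baseline adjustment. The unadjusted SE already includes this variation, so it is part of the precision loss and not a further one.

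**The case against.** The best reply is that the protocol never calls this variable an indicator. It labels binary variables when it means them: the group and phase terms are called dummies, and infections are given as two-valued data. Cognitive impairment carries no such label and sits in the model list beside functional status, which is a total score. The threshold could be read as saying that GDS scores from 2 upward count as impairment, with the score itself analysed. The stated aim of relating severity to CRB supports that reading.

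This stands in part. The graded reading is possible, and no sentence settles the matter, so it would go too far to say that the covariate is certainly a constant. But the graded reading has to override the only operational definition given, which the model section adopts by reference. The neighbouring covariate, functional status, is explicitly defined as a total score, so the authors had that wording to hand. On either reading the phrase needs correcting.

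Two further objections also stand. That all 80 residents will score 2 or more is an inference from the stage labels: entry rests on a charted diagnosis and the GDS is rated separately. It is very likely but not stated, hence *essentially every*. And the 5% to 11% reduction in SE, with its equivalent of 1/0.90 = 1.11 to 1/0.80 = 1.25 times as many residents, ignores the baseline CRB observations and the other covariates. It should not be quoted as the expected loss.

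**Conclusion.** The point holds as a defect of definition. Read literally, the covariate is met by essentially every eligible resident, carries almost no information, and contradicts the purpose given for it in the same paragraph.

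A reader might infer that the treatment comparison is biased or that the severity adjustment is certainly void. The document supports neither. Allocation is by individual randomisation, so omitting a baseline covariate does not bias the group effect, and the authors may have intended the graded stage. H1 and H2 concern the group effect and do not depend on this covariate.

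What remains is some lost precision, which includes the adjustment for chance imbalance in severity, and a severity-CRB question that the variable as defined cannot answer. The precision loss cannot be derived from the document. Under the assumptions above it is about 1% to 4% of the SE when baseline CRB is used, which is small. The near-constancy of the indicator rests on one assumption: that few or no residents with documented dementia will be rated stage 1.

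**What to change.** In Instruments and Measures, delete the threshold of 2 and state that the GDS stage rated at baseline is the level-2 covariate, entered as a graded variable (ordinal or continuous). The functional form, and any handling of sparse stages, can be left to the analysis plan. This changes one phrase. Table 1 already schedules the rating, so it needs no new data, visits or sample size, and it also lets the severity-CRB question be answered.
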